**1. Background**

Soil-transmitted helminthiasis, caused by infections with intestinal nematodes, remains among the most prevalent and debilitating parasitic diseases in the world (Horton 2003; Utzinger and Keiser 2004; Bethony et al. 2006). More than 2 billion people are infected, and there is growing evidence about the negative impact of soil-transmitted helminth infections on the course and outcome of pregnancy (i.e. anaemia), children’s physical and cognitive development, educational attainment and worker productivity in later life (WHO 2002; Miguel and Kremer 2004; Utzinger and Keiser 2004; Bethony et al. 2006; Lammie et al. 2006). Recent estimates suggest that the global burden due to soil-transmitted helminthiasis might by as high as 39 million disability-adjusted life years (DALYs), thus approaching or even surpassing the burden of malaria (Hotez et al. 2006). The major soil-transmitted helminth species are *Ascaris lumbricoides*, *Trichuris trichiura* and the hookworms (*Necator americanus* and *Ancylostoma duodenale*). They show the widest geographical distribution and current estimates are that between 807 and 1221 million people are infected with *A. lumbricoides*, 604-795 million people with *T. trichiura*, and 576-740 million people with the hookworms (Bethony et al. 2006).

There is growing recognition of the public-health significance of yet another soil-transmitted helminth, namely *Strongyloides stercoralis* (Keiser and Nutman 2004). An estimated 30-100 million people are infected (Bethony et al. 2006). However, no data is currently available regarding the global burden and geographical distribution of strongyloidiasis. An important underlying reason is that one of the most widely used diagnostic approaches for the evaluation of intestinal helminth infections – i.e. the Kato-Katz technique (Katz et al. 1972) – is unsuitable for detection of *S. stercoralis*, and microscopic examination of direct faecal smears only has a low sensitivity (Sato et al. 1995). The available methods with a high sensitivity [i.e. Koga agar plate (Koga et al. 1991) and Baermann technique (Garcia 2001)] are time-consuming and somewhat cumbersome to perform.

High prevalences of *A. lumbricoides*, *T. trichiura* and hookworms have been reported from sub-Saharan Africa and Southeast Asia, including China (de Silva et al. 2003; Bethony et al. 2006). According to the Chinese Ministry of Health (MoH) the prevalence of soil-transmitted helminth infections in Yunnan province was 21.7% during the second nationwide parasitological survey completed in 2004 (MoH 2005). Additional helminth infections are known to occur in this area, i.e. *Enterobius vermicularis*, *Taenia solium* and *T. saginata*, and the presence of various food-borne trematodes is strongly suspected. There is a lack of data for *S. stercoralis*.

In June 2006, we carried out a cross-sectional study in a small village in the southern part of the Yunnan province. Parasitological screening of 180 randomly selected individuals revealed that soil-transmitted helminth infections were pervasive; we found a point prevalence of *A. lumbricoides*, *T. trichiura* and hookworms of 93.9%, 88.9% and 87.8%, respectively. In addition, we found 21 cases positive for *S. stercoralis*, accounting for a prevalence of 11.7% (Steinmann et al. 2007). Our results implied that multiparasitism was the norm rather than the exception, confirming recent reports from Africa (Raso et al. 2004) and South America (Brooker et al. 2006).

The functional significance of multiple helminth infections on clinical outcomes (e.g. anaemia) are increasingly appreciated (Ezeamama et al. 2005) and opportunities offered for integrated control approaches have been discussed (Hotez et al. 2006; Lammie et al. 2006; Utzinger and de Savigny 2006).

Current efforts for the control of soil-transmitted helminth infections rely on chemotherapy (Lammie et al. 2006; Utzinger and de Savigny 2006). Albendazole and mebendazole are routinely used in chemotherapy campaigns targeting millions of children and adults each year. These drugs have a good safety profile and the low frequency and generally mild nature of adverse side effects even allows their use by non-medical personnel, such as school teachers in school-based mass treatment campaigns (WHO 2002). Albendazole shows high efficacies against *A. lumbricoides* and the hookworms and a moderate efficacy against *T. trichiura* (Utzinger and Keiser 2004). Unfortunately, albendazole only has a low-to-moderate efficacy against *S. stercoralis*. The standard treatment for the latter parasite is ivermectin. This drug, on the other hand, exhibits only low activity against other soil-transmitted helminths (Utzinger and Keiser 2004).

Tribendimidine is a broad-spectrum anthelminthic drug developed by Chinese scientists in the mid-1980s (Ren et al. 1987). Tribendimidine is structurally related to amidantel, which has been developed by Bayer in the late 1970s and has been effectively used against various helminths (nematodes and trematodes) in laboratory studies and clinical trials (Thomas 1979; Wollweber et al. 1979; Rim et al. 1980). Tribendimidine is licensed by the Chinese Food and Drug Administration for the treatment of human infections with *A. lumbricoides*, *T. trichiura* and the hookworms. Its safety record compares well with that of albendazole (Xiao et al. 2005), which is further underscored by recent data obtained from phase IV trials. Clinical studies revealed that tribendimidine shows promissing activity against *Taenia* spp. and *E. vermicularis*. Unpublished studies further indicate high activities of tribendimidine against *Strongyloides venezuelensis, Hymenolepis nana* and *H. diminuta* in mice and rats. The activity of tribendimidine against *S. stercoralis* has not yet been assessed.

The World Health Organization (WHO) recommends that anthelminthic drugs are administered to entire populations in case the prevalence of soil-transmitted helminths (i.e. *A. lumbricoides*, *T. trichiura* and hookworm infection) exceeds 50% (WHO 2002). Ancillary benefits are likely to occur among individuals who are concurrently infected with other parasites (e.g. *S. stercoralis*) in case the anthelminthic drug has some efficacy against these parasites. In settings where the prevalence of soil-transmitted helminthiasis is high, small studies to comparatively assess the efficacy of different anthelmintic drugs are useful and can guide subsequent policy recommendations. This issue has been documented for Vietnam, where mebendazole is the current drug of choice in the national helminth control programme, despite significantly lower efficacy when compared to albendazole (Flohr et al. 2007).

We proposed to assess the safety and efficacy of albendazole versus tribendimidine against soil-transmitted helminthiasis, including *S. stercoralis*. Our proposal is further motivated by the following considerations. First, it is plausible that tribendimidine will be used in mass treatment campaigns in China, in addition to the currently used albendazole. Since tribendimidien and albendazole belong to different chemical classes (Wollweber et al. 1979; Utzinger and Keiser 2004), alternating between the two drugs would reduce the chance of resistance development (Geerts and Gryseels 2000). Second, by default, mass treatment campaigns are not preceded by individual diagnosis of parasitic infections, and hence there is an opportunity to assess the potential ancillary benefits on other parasitic infections. Third, we lack detailed knowledge on whether multiple species parasitic infections have an effect on treatment outcomes (i.e. altered safety or efficacy profiles). Fourth, in case tribendimidine results in a higher efficacy against *S. stercoralis* than albendazole, the use of tribendimidine would offer an elegant way to cover an additional parasite, which is neglected, but nonetheless of considerable public health significance. It is important to note that ivermectin is currently not available for human use in China.

**2. Detailed research plan**

**2.1. Study aims**

(1) To further our understanding of the local epidemiology of soil-transmitted helminthiasis (including strongyloidiasis) in selected villages in Yunnan province of China.

(2) To comparatively assess the sensitivity and specificity of different diagnostic approaches for soil-transmitted helminth infections, with particular consideration to *S. stercoralis*.

(3) To assess the safety and efficacy of oral albendazole versus oral tribendimidine (both drugs will be administered in a single dose of 200 mg for children aged 5-14 years, and 400 mg for individuals aged ≥15 years) against different soil-transmitted helminth infections.

**2.2. Experimental design**

*2.2.1. Study area and population surveyed*

The study will be carried out in Nan Weng village in Menghai county, Xishuangbanna prefecture, Yunnan province, China. The village is inhabited by approximately 350 individuals of Bulang nationality, belonging to 80 families. All family members aged 2 years and above will be invited to participate in the initial parasitological screening. Participating (≥1 stool sample submitted) individuals aged ≥5 years will be enrolled in the comparative treatment efficacy study, irrespective of the parasitological diagnosis.

Based on our preliminary work in the same area we anticipate that 80-90% of the eligible individuals who are present in the village at the time of the survey will submit at least 1 stool sample and we anticipate that point prevalence with the three main soil-transmitted helminths will exceed 80%. Moreover, we anticipate that 10-15% of the individuals will harbour *S. stercoralis*.

*2.2.2. Patient inclusion criteria*

(1) Age ≥5 years, both sexes.

(2) Submission of ≥1 stool sample for the baseline parasitological survey.

(3) For females, not pregnant, as verbally assessed by medical personnel on the day of treatment.

(4) Absence of major systemic illnesses, as assessed by medical personnel on the day of treatment.

(5) Written informed consent by the head of the household on behalf of the whole family.

*2.2.3. Patient exclusion criteria*

(1) Presence of any abnormal medical condition, as judged by the medical personnel.

(2) No stool sample submitted for baseline parasitological survey.

(3) Enrolled in any other clinical investigation during the study.

(4) For females: pregnancy

Standard anthelminthic treatment according to the applicable Chinese treatment guidelines will be offered to all residents of Nan Weng village aged 2 years and above who are not included in the comparative treatment efficacy study.

*2.2.4. Baseline survey*

Demographic, economic and health-related behavioural data of the village population will be collected by means of pre-tested individual and family questionnaires. All residents aged ≥2 years will be invited to submit 3 stool samples over a 6-day period. The stool samples will be collected daily and continuously processed by the following diagnostic techniques.

(1) Kato-Katz (diagnosis of *A. lumbricoides*, *T. trichiura*, hookworms, *Taenia* spp., other helminths): 1 slide/sample.

(2) Baermann (diagnosis of *S. stercoralis*): 1 test/sample.

(3) Koga agar plate (diagnosis of *S. stercoralis* and hookworms): 1 plate/sample.

(4) Sodium acetate-acetic acid-formaline (SAF) conservation (followed by ether-sedimentation technique, to be done after conclusion of the field study; diagnosis of helminths and intestinal protozoa): 1 sample/individual

*2.2.5. Treatment*

Study participants (according to above-specified inclusion criteria) will be randomly assigned to either albendazole (group A) or tribendimidine (group B).

In group A, participants aged 5-14 years will receive a single 200 mg oral dose of albendazole; older participants will be treated with a single 400 mg oral dose of albendazole. In group B, participants aged 5-14 years will receive a single 200 mg oral dose of tribendimidine; older participants will be treated with a single 400 mg oral dose of tribendimidine. The drugs will be distributed to the study participants after dinner time (ca. 18:00 hours) by local health professionals, and ingestion confirmed.

*2.2.6. Acute adverse effect monitoring*

The treating health professionals and a medical doctor will be present in the village for the next 3 hours following drug administration and respond to requests for medical assistance in case of acute adverse events (AEs). All study participants will be invited to report AEs 24 hours post-treatment. In case of AEs, appropriate medical action will be taken, e.g. administration of drugs for relief.

AEs will be graded, and their onset and duration recorded (see Appendix 3). The intensity of AEs will be judged by the medial doctor as followed:

*Mild:* present but not requiring any interference

*Moderate:* (1) present and requiring medication for symptomatic relief as requested by the affected people or 2) present and interfering with normal daily activities.

*Severe:* present and required medical intervention beyond symptomatic relief.

.

*2.2.7. Endpoint parasitological stool survey*

2-4 weeks after the treatment, all study participants will be invited to submit another 3 stool samples over a 6-day period. The stool samples will be collected daily and continuously processed by the same diagnostic techniques as detailed above.

Participants without eggs or larvae in their stools as assessed by the respective methods will be considered parasitologically cured. Egg reduction rates for the different parasites will be calculated based on the arithmetic mean egg count of the 3 Kato-Katz slides prepared before and after treatment. Cure rates will be calculated on a per-species basis and not take into account the influence of the treatment on any co-infections.

*2.2.8. Concomitant therapy*

No restriction except antiparasitic treatment (albendazole, mebendazole, levamisole, pyrantel pamoate or any other anthelminthic drug). Participants are asked about antiparasitic treatment over the preceding month upon distribution of the study drugs.

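### Inclusion criterion 5 accepts the household head's consent for competent adult relatives and requires neither an adult's own consent nor a child's assent

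*Protocol*

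**What the plan says.** The consent condition is the fifth inclusion criterion in section 2.2.2: "Written informed consent by the head of the household on behalf of the whole family". The first criterion sets the age range, "Age ≥5 years, both sexes", so the trial population runs from young children to adults of any age.

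Section 2.2.1 describes the setting: "The village is inhabited by approximately 350 individuals of Bulang nationality, belonging to 80 families". It also describes two steps for the individual. The first is an invitation to screening: "All family members aged 2 years and above will be invited to participate in the initial parasitological screening". The second follows for anyone aged 5 or over who submitted at least one sample. Such people "will be enrolled in the comparative treatment efficacy study, irrespective of the parasitological diagnosis". Section 2.2.5 then has them randomly assigned to albendazole or tribendimidine and dosed by local health professionals, who verify that the drug is swallowed.

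The exclusion criteria in section 2.2.3 cover an abnormal medical condition, no baseline stool sample, participation in another clinical investigation, and pregnancy. A person's own refusal of the trial is not among them. Appendix 1 is listed as the informed consent sheet, but its text is not in the copy reviewed here.

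**The concern.** The criterion states a rule; this is not a case of something left unsaid. A site applying it literally may count the consent condition as met for a competent adult who has signed nothing, provided that the head of the family has signed. For children, the same signature suffices whether or not the head is the child's parent or guardian, and the child's agreement is not asked for.

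This matters because the study is research and not routine deworming. Participants are allocated at random between two drugs. Section 1 says that the activity of tribendimidine against *S. stercoralis* has not yet been assessed, and that little is known about whether multiple infections alter safety or efficacy. Those are the things an individual would need to be told before agreeing. What is at stake is the protection of participants and the ethical standing of the enrolment. No estimate or test in the protocol is affected.

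**Working it through.** The protocol states no figure on this point, so there is none to reproduce. The check is mainly a reading of the criteria together, with one division.

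**1. Whose consent is required?** Inclusion 5 names one person per household, the head, and extends that consent to the family without an age limit. Inclusion 1 admits adults as well as children. Taken together, proxy consent for competent adults satisfies the criteria.

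**2. Does another criterion require the individual's agreement?**
- Inclusion 2 and exclusion 2 require the person's own stool sample. That is participation in screening.
- Inclusion 3 and 4 and exclusions 1 and 4 are medical and pregnancy checks, for example "Presence of any abnormal medical condition, as judged by the medical personnel". They concern fitness for treatment.
- Exclusion 3 concerns enrolment in other studies.

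None of these asks an adult to consent, or a child to assent, to random allocation.

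**3. Is there an individual choice between screening and randomisation?** Section 2.2.1 uses the language of invitation for the stool survey only. The move from a submitted sample to the randomised comparison is stated as something that will happen to the person. No separate decision is described between the two.

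**4. How many people per signature?** Inputs from section 2.2.1: about 350 residents, 80 families.

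350 / 80 = 4.375, or about 4.4 residents per signature.

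This counts residents of all ages, including children under 5, who are not eligible for the drug comparison. The number of adults other than household heads is the figure that would matter most. It cannot be obtained, because the protocol gives no age distribution.

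**5. Could the consent sheet settle it?** There are two cases. If the sheet in Appendix 1 requires each adult's own consent, it contradicts inclusion 5 and the two must be brought into line. If it follows inclusion 5, proxy consent for adults is the actual rule. The criterion needs rewording in both cases.

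**The case against.** The strongest objection is that the consent sheet has not been seen. It may provide for individual information, assent or a right to decline, and nothing may be inferred from its absence here. This stands against any claim about what participants are actually told. A reader might infer from inclusion 5 that adults are dosed uninformed or against their will; the documents do not show that. It does not rescue the wording of the criterion, for the reason in step 5 of the working.

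A second objection is that the head's signature alone enrols nobody. Each person is invited to screening, must provide stool, is assessed by medical personnel and must swallow the drug. Someone who withholds stool is excluded whatever the head has signed. This is correct, and it rules out saying that the criterion enrols people who refuse to take part at all. What it leaves open is a person who gives stool for a diagnosis and has not agreed to be randomised.

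Other inferences go further than the text allows:

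- **Pregnancy.** A reader might link proxy consent to the pregnancy check, "For females, not pregnant, as verbally assessed by medical personnel on the day of treatment". That is a separate eligibility matter. Medical personnel make the assessment, and the exclusion "For females: pregnancy" stands beside it. A pregnancy that the woman herself does not know of would be missed whoever signs the consent. No count of pregnant women at risk can be derived, because the protocol gives no rates.
- **Bias.** A reader might expect unwilling members to withhold endpoint stools and so distort the comparison. This is conjecture. Those people have already given baseline stool, unwillingness that precedes assignment should be balanced by randomisation, and nothing links it to one arm. A head's refusal falls before randomisation. It may cost sample size or representativeness, but it does not bias albendazole against tribendimidine.
- **Share without their own signature.** Subtracting one signature per family gives 350 − 80 = 270 residents, or 270 / 350 = 77%. This assumes that everyone takes part, and it counts children, for whom a parent's or guardian's consent would be expected anyway. It is not an estimate of adults without their own consent.

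**Conclusion.** The point holds in a limited form. The eligibility criteria shown accept one written consent by the household head for the whole family, with no age limit. They require neither a competent adult's own consent nor a child's assent to the randomised comparison. About 4.4 residents of all ages fall under each signature; this rests only on the village and family counts in section 2.2.1. The number of adults affected is unknown.

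The conclusion concerns what the criteria permit. It assumes nothing about what the consent sheet says or how the field team would behave. The change should be made, because it protects participants at little cost, but the analysis and the validity of the drug comparison do not depend on it.

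**What to change.** Rewrite inclusion 5 so that it requires:

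- for each adult, that person's own consent, in writing or witnessed;
- for each minor, consent from a parent or guardian together with the child's assent;
- the household head's agreement, if wanted, as an additional step that does not replace either of these.

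Add individual refusal to the exclusions in section 2.2.3, and check Appendix 1 against the new wording so that the sheet and the criterion name the same people.

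The cost is an amendment of one criterion and, where needed, the sheet, plus more signatures. These can be collected at the baseline visits in section 2.2.4, where individual questionnaires and repeated stool collection are already planned. A few people may decline. Section 2.2.3 already offers standard anthelminthic treatment to residents aged 2 and above who are not in the comparison, so declining does not cost them that offer. No endpoint, treatment or analysis changes.

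### Adverse events are collected only by volunteered report up to 24 hours, with no pre-dose symptom record described, so absolute rates are hard to interpret, later events are missed and the contrast between drugs is diluted

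*Protocol*

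**What the plan says.** Section 2.1, aim 3, makes safety a comparative objective: "To assess the safety and efficacy of oral albendazole versus oral tribendimidine". The protocol's arrangements for measuring it are these.

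- **First 3 hours (section 2.2.6).** Drugs are given at about 18:00. The treating staff and a doctor "will be present in the village for the next 3 hours following drug administration" and respond when someone asks for help.
- **24 hours (section 2.2.6).** "All study participants will be invited to report AEs 24 hours post-treatment". No standard question or symptom list is described in the text.
- **Recording (section 2.2.6).** "AEs will be graded, and their onset and duration recorded", with a reference to Appendix 3, whose form is not reproduced in the copy reviewed.
- **Grading (section 2.2.6).** The doctor judges intensity. Moderate is met either by an event "requiring medication for symptomatic relief as requested by the affected people" or by interference with daily activities. Severe is defined by medical intervention going further than symptom relief.
- **Before dosing (sections 2.2.2 and 2.2.3).** Inclusion requires "Absence of major systemic illnesses, as assessed by medical personnel on the day of treatment". Exclusion covers "Presence of any abnormal medical condition, as judged by the medical personnel". Neither criterion describes a record of symptoms.
- **2 to 4 weeks (section 2.2.7).** Participants are invited to give stool samples. No AE question is described.

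**The concern.** These are choices about data collection, so an analysis plan cannot repair them later. It can define a treatment-emergent event, but it cannot apply that definition to symptoms never asked about before dosing, or supply an end date that nobody requested.

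Three things are at stake. First, each drug's AE rate becomes a mixture of drug effect, everyday complaints and willingness to report. Second, a real difference between the drugs becomes harder to see, so the two may look equally safe by default. Third, section 1 gives as one motive for the trial that it is not known whether infection with several species alters the safety profile. Infection status is not randomised. If people with more species also have more everyday symptoms, that comparison is confounded, and there is no pre-dose record with which to separate the two.

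**Working it through.** The protocol states no AE rate, background symptom rate or reporting rate, so there is no figure of its own to reproduce. The check sets the provisions side by side and then works out the direction of each effect.

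**Step 1: what is promised against what is collected.**

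| Needed for the safety aim | What is described | Gap |
| --- | --- | --- |
| Who had no event | Requests for 3 hours, one invitation at 24 hours | Silence and absence of an event look the same |
| Which symptoms are new | Same-day medical check; onset of reported AEs | People are screened out, but symptoms are not recorded; onset is recalled afterwards, by reporters only |
| Duration | To be recorded; last AE contact at 24 hours | An event still present at 24 hours has no end date |
| Later events | Stool collection at 2 to 4 weeks | No AE question, so an event starting after 24 hours is not captured |

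**Step 2: a simple model.** Let b be the risk of a background symptom, d the drug-caused risk and r the probability that a person with symptoms reports. Taking background and drug-caused symptoms as independent, the observed proportion in an arm is

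observed = r × [1 − (1 − b)(1 − d)].

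**Step 3: background equal in both arms, full reporting (r = 1).** The risk difference is (1 − b)(d_B − d_A). It shrinks as b rises and never changes sign. Illustration with assumed d = 5% and 10%, and b from 0 to 30%:

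| b (assumed) | Arm 1 | Arm 2 | Difference | Ratio |
| --- | --- | --- | --- | --- |
| 0% | 5.0% | 10.0% | 5.0 points | 2.00 |
| 10% | 14.5% | 19.0% | 4.5 points | 1.31 |
| 20% | 24.0% | 28.0% | 4.0 points | 1.17 |
| 30% | 33.5% | 37.0% | 3.5 points | 1.10 |

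For b = 20%: 1 − 0.80 × 0.95 = 0.24 and 1 − 0.80 × 0.90 = 0.28. Background raises both rates and pulls the ratio towards 1. It creates no false difference.

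**Step 4: under-reporting, equal in both arms.** A common r below 1 multiplies both rates and the difference by r and leaves the ratio unchanged. Background pushes the absolute rate up and non-reporting pushes it down, so even the sign of the net error is unknown. With d = 10%, assumed values b = 0 and r = 0.6 give 0.6 × 0.10 = 6%, while b = 20% and r = 1 give 28%.

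**Step 5: reporting that differs by arm, no true difference.** The bracket is then the same in both arms and cancels, so the observed ratio is r_B / r_A. Assumed pairs of 60% v 60%, 60% v 70%, 60% v 80% and 50% v 80% give ratios of 1.00, 1.17, 1.33 and 1.60. With b = 20% and d = 5%, the bracket is 0.24, and 60% v 80% gives 14.4% v 19.2%. This is the only route in the model to a spurious contrast, and it requires behaviour that depends on the arm.

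All rates in steps 3 to 5 are assumptions chosen to show direction. They do not estimate what would happen in this village.

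**The case against.** The strongest reply is that the comparison is randomised between two active drugs and everyone receives the same invitation at the same time. A reader might infer from the missing pre-dose record that everyday symptoms will be counted as drug effects and tilt the comparison. The protocol does not support that. Step 3 shows that balanced background favours neither drug, and nothing in the text says that every AE will be attributed to treatment.

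Other parts of the reply also stand:

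- The same-day medical check removes some people with complaints, and a recorded onset before the dose would identify some earlier symptoms. This helps only in part, for the reasons given in step 1.
- A reader might conclude that the trial is unmasked, perhaps citing the treatment column on the Appendix 2 participation form. That column may mean only treated or not treated. The available text neither describes masking nor calls the trial open-label, and some front pages are not shown.
- A reader might say that grades simply measure care received. That overstates it: interference with daily activities is a second route to moderate. Care alone decides only the severe grade. Nor does the 3-hour presence mean that care ends then, since action on AEs is also described after the 24-hour invitation.
- The Appendix 3 form may hold a symptom list, and the invitation may in practice be an interview. The text, however, cites the appendix for grading, onset and duration, not for a pre-dose interview or a later contact.
- Acute monitoring of a single dose can reasonably be short. It then does not fit with recording duration for events that outlast it.

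What remains is volunteered capture, no described pre-dose record, and a promise of duration with no described contact at which to complete it.

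**Conclusion.** The point holds as a weakness of measurement, not as a demonstrated bias towards one drug. As described, section 2.2.6 cannot separate non-reporters from people without events, cannot complete the duration of events lasting beyond 24 hours, and misses events that start later. Absolute AE rates cannot be read as drug rates, and the contrast between arms is diluted. A false difference is possible only if reporting or grading depends on the arm, which the available text does not rule out. The question of whether multiple infections alter safety is open to confounding by background symptoms.

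No numerical size can be given, because the protocol supplies none of the rates needed. The conclusion also assumes that the parts not shown (the Appendix 3 form and some front pages) do not already contain a symptom list, a later AE contact or masking of the grader.

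**What to change.** - At drug distribution, where section 2.2.8 already has participants asked about recent antiparasitic treatment, put the same short symptom list to every participant and record the answers, including none.
- Repeat the list with everyone at 24 hours, and analyse new or worsened symptoms as treatment-emergent.
- At the endpoint stool collection, add one AE question covering onset and end.
- Record medication or intervention in its own data field beside the intensity grade, so that intensity can also be analysed apart from care sought.
- Where feasible, have the existing grading doctor work from the participant ID without the allocation list.

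The cost is brief extra interview time at contacts that already exist, plus somewhat more data entry. No extra visit is needed, and clinical management is unchanged.
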